## Abstract

**Background:**

It is known that repetitive, skilled, functional movement is beneficial in driving functional reorganisation of the brain early after stroke. This study will investigate a) whether pedalling an upright, static exercise cycle, to provide such beneficial activity, will enhance recovery and b) which stroke survivors might be able to participate in pedalling.

**Methods/Design:**

Participants (n = 24) will be up to 30 days since stroke onset, with unilateral weakness and unable to walk without assistance. This study will use a modified exercise bicycle fitted with a UniCam crank. All participants will give informed consent, then undergo baseline measurements, and then attempt to pedal. Those able to pedal will be entered into a single-centre, observer-blinded randomised controlled trial (RCT). All participants will receive routine rehabilitation. The experimental group will, in addition, pedal daily for up to ten minutes, for up to ten working days.

Prognostic indicators, measured at baseline, will be: site of stroke lesion, trunk control, ability to ambulate, and severity of lower limb paresis.

The primary outcome for the RCT is ability to voluntarily contract paretic lower limb muscle, measured by the Motricity Index. Secondary outcomes include ability to ambulate and timing of onset and offset of activity in antagonist muscle groups during pedalling, measured by EMG.

**Discussion:**

This protocol is for a trial of a novel therapy intervention. Findings will establish whether there is sufficient evidence of benefit to justify proceeding with further research into clinical efficacy of upright pedalling exercise early after stroke. Information on potential prognostic indicators will suggest which stroke survivors could benefit from the intervention.

**Trial Registration:**

ISRCTN: ISRCTN45392701

## Background

### Therapy early after stroke

In the first few weeks after stroke, the brain is 'primed' for neurological recovery in response to rehabilitation training [1]. Indeed, Cramer [2] describes a 'golden period' for initiating restorative therapies, starting in the first days after onset and continuing for several weeks. However, animal studies on early therapy are equivocal. Kozlowski et al [3] demonstrated an increase in lesion size following early training and proposed a 'use-it-but-don't-overuse-it' strategy in this period. In contrast, Biernaskie et al [4] found that rats given enriched rehabilitation training from day five after an induced lesion demonstrated a marked improvement in recovery, whilst those given similar training beginning at day 30 improved no more than controls.

Whilst animal studies provide insights into brain changes underlying recovery, caution must be observed in generalising to human populations. Nonetheless, clinical studies do support early rehabilitation intervention to improve outcomes [5,6]. It is also possible that, if rehabilitation onset is delayed, patients might establish compensatory behaviours that could impact negatively on recovery of useful functional activity [7,8]. Additionally, National Clinical Guidelines for Stroke in the United Kingdom advise that people with acute stroke should be mobilised as early as possible [9]. However, the optimal dose and type of physical therapy required to drive useful functional reorganisation in early stroke survivors with different clinical characteristics remains unknown.

### Repetitive, functional training early after stroke

In the first days to weeks after onset, stroke survivors can present particular therapeutic challenges. Leg weakness is often substantial and the ability to contract paretic muscle sufficiently to be able to take part in functional, relevant activity, such as walking training, can be severely compromised. There are interventions which can be used to improve ambulatory capacity early after stroke-including treadmill training with and without partial body weight support, and walking facilitated 'hands-on' by therapists-but these are often time-consuming and likely to require extensive physical assistance from one or more members of a therapy team. The effort required from both patient and therapist(s) is often too great to enable more than a few repetitions of activity. This dose might be too low for effect.

Although the number of repetitions of an activity needed to facilitate human brain reorganisation has not been established, animal model studies suggest that 300-400 repetitions in a 30 minute session might be needed [10]. Repetition of motor activity has been demonstrated to produce changes in cortical representation maps [10,11], and may be an important consideration in rehabilitation programmes.

Repetition of motor activity alone, however, is not a sufficient driver to induce functional reorganisation of cortical networks. Motor skill acquisition, or motor learning, has been demonstrated to play a central role, in both animal [12] and human [13,14] studies. It has also been suggested that there may be benefit from goal-directed functional activity associated with normal afferent stimulation [15]. The salience of a task is an important consideration in rehabilitation programmes [7]. Indeed, current clinical guidelines suggest that functional, task specific activity is a key component of rehabilitation after stroke; gait re-training to improve independence in walking is such a functional activity and a principle goal for many patients [9]. Such evidence might suggest that optimal rehabilitation programmes should involve task specific activity and increasing levels of motor skill [16].

Therapists are therefore challenged to find strategies that enable repetitive, relevant and skilled activity in early stroke survivors. However, it remains unknown a) which specific physical therapies might drive brain reorganisation and motor recovery and b) which patients might respond best to which therapies.

### Cycling as a potential therapeutic activity early after stroke

Cycling is a functional activity that has potential to benefit patients when used as an adjunct to therapy after stroke [17]. It requires that agonist and antagonist muscles are contracted reciprocally and in a similar pattern to that required for walking [18]. Therefore, it is a repetitive muscle activity that may be beneficial in retraining gait [19]. Indeed, pedalling may facilitate phasic, co-ordinated muscle activity even in patients with severe hemiparesis [20]. Whilst familiar to many stroke survivors, reciprocal pedalling is likely to require re-acquisition of motor skill following the onset of hemiparesis.

Clinically, there is therefore potential to use static cycling for repetitive, co-ordinated exercise training as part of stroke rehabilitation programmes aiming to address deficits in motor function. However, the evidence in support of cycling interventions is preliminary. The early findings from our ongoing systematic review are that, whilst research into aerobic capacity after stroke has often incorporated a cycling paradigm [21-23], few trials have specifically evaluated the effects of cycling exercise on motor function early after stroke. There are some indications that cycling activity may have a positive effect on strength, reciprocal activation of antagonistic muscle groups and balance in stroke survivors in the sub-acute and chronic stages but cautious interpretation of these results is required for a number of reasons: sample sizes were relatively small (n = 24 [24]; n = 17 [20]; n = 8 [25]), exact time since stroke onset was not specified [24] and findings related to a single session which was not repeated over time [20].

In addition, much of this work has used a recumbent position with a standard leg cycle ergometer for cycling exercise [20,22,24,25]. Although suitable for cardiovascular training, this position does not replicate the upright posture needed for walking. We propose that cycling to provide functional training of the lower limbs early after stroke is best provided in an upright posture, in order to maximise potential for activity in major lower limb muscle groups, in a posture similar to walking. Indeed, muscle activation patterns during pedalling are not fixed and are modified according to body position [26,27] and heightened levels of activity in quadriceps and hamstrings have been demonstrated in more upright pedalling postures [26].

We have therefore adapted a standard exercise bike a) to provide trunk support in an upright pedalling posture and b) to maximise opportunities for patients with severe lower limb weakness to pedal, with use of the UniCam crank (UniCam Inc, Emerson, New Jersey, USA; see *instrumentation*). This crank enables a reduced circumference of the pedalling circle on the paretic side, where position 2 (P2) is the smallest circle and position 9 (P9) the largest (i.e normal pedalling). A preliminary study (unpublished, 2004/05, Wandsworth UK, Local Research Ethics Committee 03.0102) has demonstrated that stroke survivors can: a) pedal the modified exercise cycle for up to ten minutes with no adverse effects, and b) tolerate the different positions of the right and left pedals. Participants were included in this observational study if they were at least 14 days after stroke onset, able to sit without support for one minute, able to follow a one-stage command, previously independently mobile but now unable to mobilise and having no other limiting disease process or pathology.

### Potential prognostic indicators for therapeutic interventions

Therapists use a wide range of clinical interventions in their repertoire but there is little research evidence to guide clinical decisions on which patients are likely to respond to which therapies. Possible influential factors include the location and size of brain lesion [28,29], degree of motor weakness; and ability to control the trunk to sit independently [30,31]. It is unknown whether these factors are prognostic for obtaining benefit from pedalling exercise early after stroke.

## Aims

The driver for this proposed research is the hypothesis that UniCam crank-assisted upright pedalling (UP), used as an adjunct to conventional physical therapy, enhances recovery of lower limb motor function in stroke survivors with substantial paresis early after stroke. However, before this hypothesis can be tested in a phase III trial, it is important to establish whether there is sufficient evidence of benefit (clinical efficacy) to justify proceeding to subsequent larger trials and which stroke survivors are most likely to be able to participate in UP (prognostic indicators). Therefore, the aims for the current early phase clinical research study are:

1. Clinical Efficacy

To determine whether there is sufficient evidence for UP, balancing efficacy and potential adverse events (pain and fatigue), to justify proceeding to subsequent larger clinical trials; as assessed by:

a) ability to voluntarily contract paretic muscle;

b) production of reciprocal activation of antagonistic muscle groups during pedalling, similar to walking;

c) timing of onset and offset of activity in antagonist muscle groups during pedalling, similar to walking;

d) ability to walk independently.

2. Prognostic Indicators

To determine whether site of stroke lesion, trunk control ability, severity of lower limb paresis and/or ambulatory ability predicts ability to use UP within 30 days of stroke onset.

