### Participant inclusion criteria and recruitment process

Participants will be recruited from an acute stroke unit and, if necessary due to pressure on stroke beds, medical wards; in a University Hospital Trust. Consultant and therapy teams have agreed to support this trial.

Stroke survivors will initially be approached by a clinical team member responsible for their care, to check that they agree to speak to a researcher. If they agree, then a researcher will provide potential participants with verbal and written printed information about the trial. A video of the procedure for getting on and off the exercise cycle will also be available if patients wish to view it. A minimum of twenty four hours (1 working day) later, informed, signed consent will be sought. Those providing written informed consent will be participants in this trial. All potential participants will then be screened to check that they meet the study criteria, which are;

• adults aged 18+

• three to thirty days following a unilateral stroke resulting in unilateral muscle weakness with or without sensory deficit;

• fit to participate as assessed by a consultant-led medical team with resting oxygen saturations 95% or above, resting heart rate 90 beats per minute or less and systolic blood pressure of 100-160 mmHg

• score 0, 1 or 2 on the Functional Ambulation Categories [32]. Clinically, this means unable to walk; or need the help of two or more people; or require firm continuous or intermittent support of one person assisting with weight and balance;

• be able to sit unsupported for 30-seconds on the edge of a bed with feet on the floor.

• have sat out of bed in a chair or wheelchair at least once for a continual period of 15-minutes i.e. have appropriate sitting tolerance to participate in this cycling intervention;

• be able to follow a one-stage command i.e. sufficient communication, orientation and memory to participate in this cycling intervention;

• be independently mobile with or without an aid prior to the index stroke;

• have no co-existing pathology contributing to observed impairment in the paretic lower limb e.g osteoarthritis with associated knee deformity.

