##### Secondary outcomes

2. Ability to walk independently

As measured by the Functional Ambulation Categories (FAC) [32]. This scale is designed to give detail on physical support needed by patients for walking, so has clinical relevance, and is easy to use. It has established validity and reliability for use after stroke [38]. It is an ordinal scale, patients scoring from 0-5, where 0 indicates a patient who is not able to walk or needs help of 2 therapists, and 5 indicates a patient who is independent in ambulation even on stairs.

3. Onset and offset of EMG activity of antagonistic muscle groups during pedalling

EMG activity will be recorded in quadriceps and hamstring muscles for each leg. Before getting on the bike, participants will have a small (37 mm × 18 mm) pre-amplifier applied to the front and back of their thigh on both sides, following skin preparation to minimise signal interference. Electrode position is known to be a vital factor in achieving accurate EMG information [39]. For this study, a single researcher will place the electrodes for each participant and for every session, using published guidelines [40]. When the participants are positioned comfortably on the bike, the leads from the pre-amplifiers will be connected as described in *instrumentation*.

Resting EMG activity will be recorded as a voltage at 1,000 Hz whilst the participant's foot is resting firmly on a box so that the leg is still and supported with the knee in 5-15 degrees of flexion, for 30 seconds. This will be undertaken for each leg. EMG data (voltage) will be collected continuously during pedalling for a minimum of 30 seconds at approximately 50 rpm.

Baseline EMG values will be calculated from the rectified, processed signal as the mean ± 3 SD (standard deviations) during the 30 seconds baseline data collection period. Onset of activity in each of the four muscle groups will be defined as the time point during the 360 degree turn at which EMG voltage exceeds the mean baseline value plus 3SD for 20 consecutive data points (20 ms). Offset of activity in each of the four muscle groups will be defined as the time point during the 360 degree turn at which EMG voltage falls below the mean baseline value minus 3SD for 20 consecutive data points (20 ms). The time point for onset and offset of muscle activity in each of the four muscle groups will also be recorded as a function of the position of the pedal during the 360 degree turn.

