## Statistical Analysis

The aim of the analysis is not to definitively demonstrate efficacy in this early phase trial. Rather the data will be used to inform a decision on whether or not to undertake subsequent studies of UP. Assuming a normal distribution, independent t-tests will be used to compare groups between trial arms for follow-up measures, together with 95% confidence intervals to inform preliminary conclusions on clinical benefit. Within-group analysis will be assessed using paired t-tests. If a normal distribution cannot be assumed, analogous non-parametric methods will be used.

Associations between potential prognostic indicators and the ability to pedal will be examined using Fishers Exact test.

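### Aim 1c counts EMG timing as evidence for proceeding, but the timing outcome has no reference or direction of benefit, so a between-arm difference cannot be read as improvement

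*Protocol article*

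**What the plan says.** The Aims section of the protocol article says the case for larger trials is to be judged on four items. Two are EMG items: 1b, "production of reciprocal activation of antagonistic muscle groups during pedalling, similar to walking", and 1c, "timing of onset and offset of activity in antagonist muscle groups during pedalling, similar to walking".

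Under Secondary outcomes, "EMG activity will be recorded in quadriceps and hamstring muscles for each leg". Apart from a resting recording, the signal is taken on the cycle: "EMG data (voltage) will be collected continuously during pedalling for a minimum of 30 seconds at approximately 50 rpm". Onset and offset are threshold crossings in time, and each "will also be recorded as a function of the position of the pedal during the 360 degree turn". No target value, reference pattern or better direction is given. Reciprocal activation (item 4) is a Spearman correlation with stated meanings at +1, 0 and -1, where -1 is full reciprocal activation.

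Under Statistical Analysis, "independent t-tests will be used to compare groups between trial arms for follow-up measures", with 95% confidence intervals, paired t-tests within arms, and non-parametric analogues if normality fails. Participants enter with a "score 0, 1 or 2 on the Functional Ambulation Categories". The experimental arm pedals for up to ten minutes on up to ten working days; the control arm receives conventional therapy only.

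**The concern.** An onset angle is not a score. Earlier onset is an improvement for someone who activates late and a deterioration for someone who activates early. Without a reference point, the sign of a mean difference between arms says nothing about benefit. If treatment pulls both kinds of participant towards the correct point, the spread shrinks while the mean may not move, and a test of means does not look for that. Changing from time to pedal angle does not help, and the paired tests within arms share the weakness.

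The second problem concerns both EMG outcomes. The outcome is measured on the apparatus that one arm has trained on and the other has met only at assessments. A between-arm difference may reflect familiarity with the cycle rather than motor recovery.

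Both matter because the Aims make these outcomes inputs to the decision on further trials. A timing difference could be taken as support when it is a move away from normal, and a real normalisation could go unseen.

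**Working it through.** **Sample size.** The protocol's figure reproduces: 2 participants per month × 12 months = 24. That is at most 12 per arm, since only those able to pedal are randomised. No SD, effect size or power is stated for any outcome, so the SDs and biases below are assumptions.

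**Aim 1c, raw timing.** Let each participant's onset error be the signed distance in degrees from the correct angle. Controls have mean bias b and SD 40. Treatment halves every error, giving mean b/2 and SD 20.

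- Expected mean difference = b − b/2 = b/2.
- Standard error with 12 per arm = √((40² + 20²)/12) = √(2000/12) = 12.9 degrees.

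| Shared bias b | Mean difference | Difference / SE | Rejection, two-sided 5% t-test (simulated) |
|---|---|---|---|
| 0 | 0 | 0 | 5% |
| 15 | 7.5 | 0.58 | 9% |
| 30 | 15 | 1.16 | 21% |
| 40 | 20 | 1.55 | 32% |

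In every row each error has been halved. In the first row the result is no more than chance. In the others the test has some power, but the reader still needs the correct angle to know whether the shift is good. The Mann-Whitney fallback does no better when errors balance (about 5% to 6%).

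**Aim 1c, deviation from a reference.** With b = 0, the mean absolute error is SD × √(2/π) = 0.798 × SD, so 31.9 degrees in controls and 16.0 in treated participants. This measure has a direction: smaller is better. How well it detects the change depends on the reference (12 per arm, SD 40 v 20, Welch t-test):

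| Reference | Rejection |
|---|---|
| Unbiased, 10 degrees of noise | 39% |
| 30-degree bias, 10 degrees of noise | 11% |
| Unbiased, 30 degrees of noise | 15% |
| 30-degree bias and 30 degrees of noise | 8% |

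With 8 per arm and the good reference, the figures are 5% for raw timing and 23% for deviation.

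**Aim 1b.** The correlation runs from +1 to -1, so a shift towards -1 can be read directly. With an assumed SD of 0.3 and 12 per arm, power is about 37% for a shift of 0.2 and 90% for 0.4. No value of the correlation in walking is given, so likeness to walking is not tested.

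**Exposure to the cycle.** Experimental arm: up to 10 × 10 = 100 minutes of training on it. Control arm: assessments only.

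**The case against.** A reader might infer that two of the four efficacy criteria cannot be answered. The documents do not support that: 1b has an anchored scale, and a move towards -1 means more reciprocal activation.

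A reader might also treat likeness to walking as a formal hypothesis left without a comparator. More probably it is rationale. The Background says that in cycling, muscles are "contracted reciprocally and in a similar pattern to that required for walking", the rationale for the clinical measures and the Discussion repeat the idea, and the outcome headings omit it. The wording is ambiguous, and that ambiguity is reason enough to tidy it.

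Nor is it true that no possible reference is recorded, because the non-paretic leg is. The protocol, however, never names it as a reference for timing. The Discussion mentions it only for detecting compensation in sessional recordings. It is a debatable reference: the UniCam crank reduces the circle on the paretic side only, and the unaffected leg may be driving the crank.

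The 5% figure is the least favourable case for the raw test, and nothing in the protocol says errors will balance; hence the range above.

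The protocol disclaims definitive efficacy, sets no EMG significance rule for proceeding, and makes the Motricity Index primary. This limits the consequence. A full protocol or SAP might name an EMG comparator. Even so, the aim and the outcome definition are both stated here, and the second does not supply what the first needs.

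**Conclusion.** The point holds for Aim 1c. As written, the plan yields a timing difference that cannot be interpreted as benefit, and it can miss a real normalisation: about 5% rejection when early and late errors balance, and 9% to 32% when they share a bias of 15 to 40 degrees (12 per arm, SD 40 v 20, all assumed). The lack of direction follows from the definitions and does not depend on these assumptions; only the percentages do.

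For Aim 1b, the only gap in the measure is that likeness to walking is untested. For both EMG outcomes, unequal practice on the test apparatus means a between-arm difference cannot by itself be read as recovery. These are secondary outcomes in an early phase trial, but the Aims count them towards the decision to proceed, so the change should be made.

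**What to change.** 1. Remove the comparison with walking from Aims 1b and 1c, or mark it as rationale. State that 1b improves towards -1.
2. For 1c, keep the raw pedal angles as description. Add, as the directional measure, the absolute angular deviation of each paretic onset and offset from a reference named in advance. The same muscle in the participant's non-paretic leg, shifted by half a turn, needs no new data. Label it exploratory, because that leg may compensate and may pedal a different circle; an error of that kind can remove most of the gain (39% down to between 8% and 15% in the cases above).
3. State that between-arm EMG differences describe pedalling performance and mechanism, and that the Aim 1 conclusion on recovery rests on the Motricity Index and FAC, which are measured off the cycle.

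The cost is protocol wording and one more derived variable with an imperfect reference. EMG would also carry less weight in the decision to proceed.
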